#### Withdrawal and Loss to Follow-Up

Participants are free to request withdrawal from the study at any stage without providing a reason. The number of participants who withdraw due to reasons such as serious adverse events, safety concerns, or the development of health conditions or symptoms is reported for each randomly assigned group at all outcome measurement time points.

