#### Secondary Outcomes

Analysis of continuous secondary outcomes will be conducted in a manner similar to that used for the primary outcome. For continuous variables such as blood-based metabolic risk biomarker variables, additional Fitbit device–measured variables, and laboratory assessment variables, we will perform an ANOVA test or, if parametric assumptions are not met, a Kruskal-Wallis test. To analyze differences in categorical variables, such as smoking status and psychological variables related to T2D genetic risk communication, we will conduct chi-square tests.

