#### Safety Considerations

This is a low-risk trial and is not expected to have any major adverse effects on participants’ health. The Physical Activity Readiness Questionnaire plays a key role in identifying risk factors such as cardiovascular conditions and musculoskeletal problems. Research staff can assess participants’ health status and reduce the likelihood of injuries and other adverse events. As no adverse events are expected from participating in any of the interventions, formal monitoring of adverse events will not be conducted. However, participants may exhibit some degree of discomfort, distress, or psychological concerns regarding their genetic risk for T2D. To address this potential issue, we aim to assess participants’ psychological responses to genetic risk communication via web-based questionnaires, which will be administered at all 4 measurement time points. Participants in the intervention groups may also misinterpret genetic risk estimates. To mitigate this, representation of diabetes risk will be assessed using the Brief Illness Perceptions Questionnaire, which consists of 9 items designed to assess cognitive and emotional representations of illness. More detailed descriptions can be found in Multimedia Appendix 1 [25,27-36]. All participants are informed of the full scope and content of the study before participation and are told that they may withdraw from the study at any time without providing a reason.

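### Psychological responses to genetic risk are to be compared by chi-square test, which for any ordered score is valid but has low power for small to moderate rises and gives no directional estimate

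*SAP article*

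**What the plan says.** The Secondary Outcomes section under Analysis Methods sets different rules by type of variable. For one type it says: "Analysis of continuous secondary outcomes will be conducted in a manner similar to that used for the primary outcome". That points to the linear mixed model with time, group and their interaction. The psychological variables are placed in the other type: for "categorical variables, such as smoking status and psychological variables related to T2D genetic risk communication, we will conduct chi-square tests". No ordinal method, baseline term or repeated-measures model is named for them.

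Safety Considerations explains why these variables matter. It states that "formal monitoring of adverse events will not be conducted", accepts that participants may be distressed by their genetic risk or misread it, and gives the response to distress: "we aim to assess participants’ psychological responses to genetic risk communication via web-based questionnaires, which will be administered at all 4 measurement time points". For misreading it names an illness-perception questionnaire, "which consists of 9 items designed to assess cognitive and emotional representations of illness". Table 1 confirms that the psychological variables are collected at baseline and three later time points. Response formats and scoring are left to Multimedia Appendix 1, which is not shown.

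One further source of safety information exists. Withdrawal and Loss to Follow-Up reports by group, at every time point: "The number of participants who withdraw due to reasons such as serious adverse events, safety concerns, or the development of health conditions or symptoms".

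**The concern.** The question these questionnaires must answer has a direction: did telling people their genetic risk make them more worried, or shift their view of the illness for the worse, compared with control? A chi-square test on an arm-by-category table asks only whether the distributions differ in any way. It treats adjacent and distant levels alike, makes no use of the score each person gave before disclosure, and does not link the four visits. It also gives none of the adjusted between-group estimates with 95% CIs that Statistical Principles promises.

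The stake is how a null result is interpreted. If the test has little chance of showing a small to moderate rise in distress, a non-significant result says little. With no formal adverse-event monitoring, there is not much else to set beside it.

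**Working it through.** **The plan's own figures.** The plan gives no sample size or power for the psychological variables, so there is no stated power to reproduce. The Sample Size section gives the number available:
- Analysis sample for the Fitbit outcome: 355 − 71 (attrition) − 36 (Fitbit data missing) = 248, as stated.
- After attrition only: 355 − 71 = 284. This is the more apt number for web questionnaires, which do not depend on the device.

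Allocation is 1:1:1 (Randomization), which gives 82 whole participants per arm at 248 and 94 at 284. The significance level is 5%.

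**Assumptions not in the documents.** An ordered response with 5 or 11 levels; a shift of d SD in both intervention arms against control; baseline correlation 0.3, 0.5 or 0.7; levels used evenly or (N = 248, correlation 0.5) skewed towards the low end. One post-disclosure visit is compared, so any gain from modelling the later visits together is not counted.

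**Why power is lost.** The chi-square test on 3 arms by K levels has (3 − 1)(K − 1) degrees of freedom: 8 for K = 5 and 20 for K = 11. A comparison of mean score or mean rank across three arms has 2. Adjusting for baseline then reduces the residual variance of a linear score by a factor of about 1 − r², for example 1 − 0.5² = 0.75.

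**Simulated power** (1,000 runs per scenario). The baseline-adjusted analysis is an F test for arm with the baseline score as covariate. At N = 248:

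| Shift in both intervention arms | Chi-square, all levels | Kruskal-Wallis (order, no baseline) | Baseline-adjusted |
|---|---|---|---|
| 0.2 SD | 9-14% | 20-25% | 24-40% |
| 0.3 SD | 15-28% | 42-48% | 47-72% |
| 0.4 SD | 30-47% | 64-75% | 72-94% |
| 0.5 SD | 47-69% | 84-91% | 90-99% |
| 0.6 SD | 71-86% | 96-98% | 98-100% |

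At N = 284, correlation 0.5 and even use of levels:

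| Shift | Chi-square, all levels | Baseline-adjusted |
|---|---|---|
| 0.3 SD | 21-28% | 59-64% |
| 0.4 SD | 38-51% | 86-89% |
| 0.5 SD | 58-77% | 97-98% |

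With no shift, rejection rates were about 4-6% for both methods, so the chi-square test is not invalid.

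If the score is first split in two at the top third, chi-square power at N = 248 is 30-34% at 0.3 SD, 51-58% at 0.4 SD and 72-76% at 0.5 SD. That is better than keeping all levels, but still below the baseline-adjusted analysis.

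**The case against.** Several things can fairly be said for the plan.

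- **The response format is not visible.** It is in an appendix that is not shown. Some variables may be truly nominal, and a scale scored as continuous might fall under the rule for continuous outcomes. This stands in part: that the scores are ordered is an inference from the description of a 9-item instrument. But the text names the psychological variables as a class among the categorical ones, so on its wording the continuous rule does not reach them. The loss of baseline and repeated visits applies whatever the format.
- **The loss is of efficiency, not validity.** This stands. In a randomised comparison, leaving out baseline costs precision and does not bias the contrast between arms. The proportions behind the test would still show a direction to anyone who read them, although the plan names no estimate of it.
- **The size depends on assumptions.** A reader might infer that a real rise in distress would usually be missed. The documents do not support this, because they give neither the size of rise nor the number of levels. At N = 248 with all levels kept, chi-square power is below 50% up to about 0.4 SD, but 47-69% at 0.5 SD and 71-86% at 0.6 SD. With a two-level split it is already above 50% at 0.4 SD. At 0.2 SD even the baseline-adjusted analysis usually misses the rise (24-40%), so that miss is not due to the test alone.
- **The questionnaires are not the only safety information.** A reader might infer that they replace all adverse-event monitoring. They address psychological responses only, and withdrawals for safety reasons are reported by group.

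**Conclusion.** The concern holds in a limited form. The plan assigns chi-square tests to the psychological variables, which are its main planned evidence on distress and misread risk after genetic risk communication. For any ordered score this discards order, the pre-disclosure baseline and the repeated visits, and yields no directional effect estimate. Power is low for small to moderate rises. At 0.3 SD it is roughly half or less of what a baseline-adjusted analysis gives, and the gap persists with the larger sample left after attrition only. At 0.4 SD and N = 248, order alone accounts for the larger part of the loss, as the Kruskal-Wallis column shows.

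These figures rest on an ordered response with 5 or 11 levels, equal shifts in both intervention arms and a baseline correlation of 0.3 to 0.7. None of these is given in the documents. For rises of about 0.5 SD or more the chi-square test would often succeed, though it would still give no estimate of the size or direction of the effect.

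**What to change.** In the Secondary Outcomes section under Analysis Methods:
- Keep chi-square for truly nominal variables only.
- Analyse the illness-perception scores and other ordered psychological scores with the longitudinal mixed model already specified for the primary outcome, or a proportional-odds version for single ordinal items. Include the baseline score and state how it enters the model.
- Report each intervention arm minus control with a 95% CI, and state in advance for each score which direction is the worse response.

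The data are already scheduled at all four time points, so no visit or participant is added. The cost is revised wording and a few extra model runs. Because formal analysis was scheduled from April 2025, the change should be dated and labelled as made at that stage.

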#### Sensitivity Analysis and Missing Data

We will conduct two sets of sensitivity analyses: (1) without adjustment for confounders and (2) using an iterative Markov chain Monte Carlo multiple imputation procedure to handle missing data at the 12-month postintervention and 6-month follow-up time points. This procedure assumes that data are missing at random within each group. The randomness of missing data will be tested using the *Amelia* package in R. For variables with missing values (eg, sex, age, educational level, BMI, blood pressure, and handgrip strength at baseline), 5 imputations will be generated for each missing value. To account for nonlinear trajectories in PA patterns, we will conduct additional sensitivity analyses using nonlinear mixed effects models with spline terms to capture nonlinear trajectories in outcome variables.

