### Sample Size

To ensure sufficient statistical power, we intend to recruit 355 East Asian participants with overweight or obesity. An oversampling strategy has been adopted, with 35.1% (87/248) of the full sample consisting of individuals at a higher genetic risk for T2D. The required number of participants (n=87) for subsample analysis was based on the desired medium effect size (*F*=0.3085), derived from a 3-group comparison. The control group’s average wearable device–measured MVPA time was 80 (SD 35) min/d. The intervention group receiving genetic risk information alone (intervention arm 1) demonstrated minimal changes (85 min/d), while the intervention group receiving combined genetic risk information and wearable device functions (intervention arm 2) was expected to show a difference of approximately 23% in MVPA time (105 min/d; [(105 − 85) / 85 × 100%], corresponding to a difference of 23% in MVPA time compared to previous Fitbit interventions) [26].

Our sample size calculation assumed an α level of 5%, a power of 80%, and a correlation of 0.70 among 3 repeated measures. A total of 355 participants are recruited to ensure the inclusion of an analysis sample of 248, while factoring in an expected attrition rate of 20% (71/355) and an anticipated Fitbit data missing rate of 10.1% (36/355), independent of attrition, considering instances of insufficient battery life or device loss.

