### Analysis Populations

Primary outcome analysis will be conducted according to intention-to-treat principles. Participants with missing outcome data at the 6-month follow-up will be excluded from the analysis.

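### The planned test of missing-data randomness cannot support missing at random, and no analysis examines informative loss of MVPA data

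*SAP article*

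**What the plan says.** Under Sensitivity Analysis and Missing Data, the SAP article plans a Markov chain Monte Carlo "multiple imputation procedure to handle missing data at the 12-month postintervention and 6-month follow-up time points". It adds: "This procedure assumes that data are missing at random within each group". The next sentence begins "The randomness of missing data will be tested" and names an R package, but gives no null hypothesis and no action that depends on the result. Then "5 imputations will be generated for each missing value"; the examples listed with it are baseline characteristics such as age, BMI and handgrip strength.

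The same section plans two other sensitivity analyses: a model without confounder adjustment, and "nonlinear mixed effects models with spline terms to capture nonlinear trajectories in outcome variables". Neither concerns missing data.

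Analysis Populations calls the primary analysis intention to treat and then says: "Participants with missing outcome data at the 6-month follow-up will be excluded from the analysis". Sample Size expects 71 of 355 participants (20%) to be lost to attrition and a further 36 (10.1%) to lack Fitbit data, leaving 248. Adherence and Protocol Deviations provides for battery and synchronization checks, reminders, and a post hoc comparison of consistent with inconsistent wearers.

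**The concern.** Missing at random and missing not at random differ only in how loss depends on values nobody saw. Because the testing sentence follows the missing-at-random assumption, its natural reading is a check of that assumption, and a non-significant result could be reported as support. It would not be support. If missing completely at random was meant, a test is possible, but passing it still does not establish missing at random. The text needs correcting on either reading.

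The gap matters because wearing, charging and synchronizing the device decide whether MVPA is observed at all. A participant who becomes inactive may plausibly also stop wearing it. Only intervention arm 2 has step goals and activity prompts, so engagement with the device, and hence loss, could differ by arm. This is a reasoned risk; the document gives no data on it. At stake is a claim of robustness that no planned analysis could have contradicted.

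**Working it through.** **1. The plan's own loss figure.** Inputs from Sample Size: 355 recruited, 71 lost to attrition, 36 without Fitbit data. 355 − 71 − 36 = 248, as stated. Share missing g = (71 + 36)/355 = 107/355 = 0.301.

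**2. Can observed data separate the mechanisms?** A simulation of 2,000,000 people in one arm used SD 35 min/d and correlation 0.70 (both from Sample Size; the correlation is applied to baseline and follow-up) with 30.1% missing. Missing follow-up values were predicted by regression on baseline among those observed, which is what missing at random implies here. The strength of each mechanism is an illustrative choice: log-odds of loss fall by 0.7 per SD of baseline, or by 1.0 per 35 min/d of follow-up.

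| Loss depends on | Baseline gap, lost minus observed (SD) | Error in raw completer mean (min/d) | Error after missing-at-random prediction (min/d) |
|---|---|---|---|
| nothing | 0.00 | 0.0 | 0.0 |
| baseline | −0.64 | +4.7 | 0.0 |
| follow-up value | −0.59 | +8.9 | +4.9 |
| only the part of follow-up that baseline does not predict | 0.00 | +4.9 | +4.9 |

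Rows 2 and 3 look almost alike in the observable comparison, yet imputation is right in one and wrong in the other. Row 4 looks like completely random loss and is still wrong. Row 2 also shows what the imputation does achieve: it removes the completers' error when loss follows an observed value.

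**3. Size of an arm-specific departure (illustrative).** Let missing arm 2 values lie d min/d below their missing-at-random prediction, with the comparator unshifted and equal loss in both arms. Overstatement = g × d.

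- d = 5: 0.301 × 5 = 1.5 min/d
- d = 10: 0.301 × 10 = 3.0 min/d
- d = 20: 0.301 × 20 = 6.0 min/d

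**4. Shift at which significance is lost.** Two-sided tests are assumed. Participants per arm: 355/3 = 118.3 randomised and 118.3 × (1 − 0.301) = 82.7 observed. SE = 35 × √(2/82.7) = 5.44 min/d, for a single-visit comparison without adjustment for baseline, and taken as unchanged by the shift. Tipping shift d* = (D − z × SE)/g, with z = 1.96, or 2.394 for Bonferroni over three pairs (thresholds 10.7 and 13.0 min/d).

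| Difference D (min/d) | d* at 0.05 | d* with Bonferroni |
|---|---|---|
| 25 (105 vs 80) | (25 − 10.67)/0.301 = 48 | (25 − 13.03)/0.301 = 40 |
| 20 (105 vs 85) | (20 − 10.67)/0.301 = 31 | (20 − 13.03)/0.301 = 23 |
| 15 (assumed) | (15 − 10.67)/0.301 = 14 | (15 − 13.03)/0.301 = 6.5 |

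**5. Number of imputations.** If the fraction of missing information equals g, relative efficiency with five is 1/(1 + 0.301/5) = 0.943, so the SE is √(1 + 0.301/5) = 1.03 times its limit. With 30 imputations, relative efficiency is 1/(1 + 0.301/30) = 0.990. Correlated visits would lower the fraction, so these are upper-end costs.

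**The case against.** The word randomness may mean missing completely at random, which observed data can reject, and no decision rule ties the result to the imputation. That is a fair reading, but it leaves the imputation's own assumption unsupported and the sentence still unclear.

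A reader might infer that the plan has no other sensitivity analysis, or that the imputation merely repeats the primary model's assumption. Neither holds. Unadjusted and spline analyses are planned. The primary analysis excludes participants without 6-month data, so imputation does relax that restriction; there is at present no all-data mixed model for it to duplicate.

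A reader might also infer that five imputations make the result hostage to the random seed. The five are tied by example to baseline variables, and whether they extend to MVPA is not explicit. Even if they do, the cost is about 3% in standard error. This is a minor point.

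Nor do the figures show that the trial's planned result is fragile. The shifts are assumptions, equal shifts with equal loss in both arms would cancel, and overturning the planned 20–25 min/d differences takes shifts of about 23 to 48 min/d.

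Finally, device monitoring, reminders, the wear-time comparison, and the reporting of exclusions with reasons and of withdrawals by group all bear on missing data. They may reduce or describe loss, but none varies the assumption about the unseen values. The lack of such an analysis is a choice of method in a section that spells its methods out, so it is fair to comment on.

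**Conclusion.** The point stands in a limited form. The stated test cannot justify missing at random, and no planned analysis addresses informative loss, although 30.1% loss is built into the sample size. The possible overstatement is about 0.30 min/d for each 1 min/d by which missing arm 2 values fall below prediction, given equal loss across arms and no shift in the comparator. An effect as large as planned would survive moderate departures. An effect nearer the significance threshold of 10.7 min/d (13.0 with Bonferroni) might not, and the present plan would not reveal it. The change should be made before robustness is claimed; it does not by itself invalidate the primary estimate.

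**What to change.** - Replace the test with a description of missingness by arm, visit and baseline covariates.
- State missing at random as an assumption that the data cannot verify.
- Fit the mixed model to all randomised participants with any MVPA data, in place of the exclusion in Analysis Populations.
- Add a delta-adjusted (tipping-point) multiple imputation of MVPA: lower the imputed values by arm in steps, for example 5 min/d, until the conclusion changes. Include arm, baseline MVPA and MVPA at all visits in the imputation model.
- Minor: say whether the five imputations cover MVPA; if so, use about 30 to 40.

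The cost is a few lines of code and one more table, which may weaken the claim. No new data are needed. The abstract says formal analysis started in April 2025, so if it has begun, the addition should be labelled as made late.

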#### Safety Considerations

This is a low-risk trial and is not expected to have any major adverse effects on participants’ health. The Physical Activity Readiness Questionnaire plays a key role in identifying risk factors such as cardiovascular conditions and musculoskeletal problems. Research staff can assess participants’ health status and reduce the likelihood of injuries and other adverse events. As no adverse events are expected from participating in any of the interventions, formal monitoring of adverse events will not be conducted. However, participants may exhibit some degree of discomfort, distress, or psychological concerns regarding their genetic risk for T2D. To address this potential issue, we aim to assess participants’ psychological responses to genetic risk communication via web-based questionnaires, which will be administered at all 4 measurement time points. Participants in the intervention groups may also misinterpret genetic risk estimates. To mitigate this, representation of diabetes risk will be assessed using the Brief Illness Perceptions Questionnaire, which consists of 9 items designed to assess cognitive and emotional representations of illness. More detailed descriptions can be found in Multimedia Appendix 1 [25,27-36]. All participants are informed of the full scope and content of the study before participation and are told that they may withdraw from the study at any time without providing a reason.

## Results

This study was funded in January 2023, and baseline data collection began in February 2023. The recruitment of 355 participants was completed in August 2023. As of February 2025, the study had entered the 6-month follow-up stage. Formal data analysis will start in April 2025 after the 6-month follow-up assessments have been completed. We expect the results to be published in December 2025.

## Discussion

### Summary

We hypothesize that intervention arm 1 will show minimal increases in objectively measured MVPA time, whereas intervention arm 2 will demonstrate significantly increased MVPA time not only at the 12-month postintervention time point but also at the 6-month follow-up.

